#### Randomization

Randomization will occur at the level of the home visiting supervisor. Supervisors will be randomized by study personnel who will not complete follow-up data collection. Using a sequence generated by study statistician, randomization will occur in permuted blocks of 4 and 6 and will be stratified by state. Allocation to intervention arm will remain concealed until inclusion and exclusion have been determined. This approach minimizes potential for experimenter and participant bias by protecting the randomization sequence and maintaining concealment of intervention allocation until the last moment. The home visiting supervisors will be aware of the trial and whether they are receiving training in adapted facilitation or in the control group. However, the home visitors and HVP recipients will not be aware there is an CRT in process so will not know to which treatment group they have been allocated or if they are not included in the cRCT.

### Trial data collection and analysis

The first objective is to analyze the uptake of MB by home visitors who receive adapted facilitation from their supervisors compared to those home visitors who receive standard support from their supervisors and those supervisors who refuse participation. This rapid ethnographic assessment (REA) will involve collecting qualitative and quantitative data (i.e., semi-structured interviews, observations, FGDs, questionnaires, and geospatial data) concurrently and iteratively and triangulating the results [27, 57, 58]. The questionnaires will allow us to measure implementation outcomes in real time and the qualitative data will provide a more nuanced understanding of why and how MB will be more readily adopted by certain home visitors, in certain HVP models, and whether delivery of the intervention varies for populations with different characteristics. As a secondary outcome, we will investigate which contextual factors identified in Aim 1 mediate or moderate the impact of adapted facilitation on implementation outcomes. The geospatial data will provide measurable indicators that will allow us to investigate the mediating or moderating effect of structural and systemic factors. We will also be able to examine factors that impact the choice of home visitor supervisors to participate in the CRT and how that impacts adoption and fidelity of MB among home visitors that are not part of the CRT.

### Qualitative component

#### Semi-structured interview and FGD guides

The research team will refine guides for the FGDs and interviews based on literature review, the iPARIHS and CFIR 2.0 frameworks, and any in vivo topics that may emerge from the Aim 1 formative evaluation. The guides will then be pilot tested with nonparticipants at partner organizations familiar with the topic and experiences of home visiting. This pilot testing will ensure that the questions are comprehendible and relevant to the Iowa and Indiana contexts. Research team members will conduct in-person or virtual interviews based on participant preferences and scheduling availability. The FGDs and interviews will be recorded, transcribed, and reviewed for accuracy. All transcripts will be analyzed using MAXQDA, secure qualitative data software [59].

#### Ethnographic observations

We will leverage existing meetings and site visits currently being conducted by IDHHS and IDOH with a combination of in-person and audio-recorded observations of: 1) weekly meetings between supervisors and visitors across all clusters in both arms to assess supervisor practice of adapted facilitation compared to standard implementation; 2) the existing biannual site visits conducted by the departments of health across a sample of models and staff, one of which is for monitoring, compliance, and needs assessment and the other for shadowing home visits, attending parent group meetings, etc. We will also attend or record monthly contractor calls, quarterly home visitor expert panel meetings, and quarterly participant advisory meetings.

##### Data analysis

The qualitative analysis team will conduct qualitative analyses using both deductive rapid and inductive in-depth methods. The analysis team will complete a *rapid ethnographic analysis* (e.g., template analysis, document review, etc.) throughout the data collection period to allow for real-time actionable adaptions to ongoing facilitation, and understand processes about MB and other main themes in a timely way [27, 57, 58]. Using a template developed with deductive, a priori iPARIHS and CFIR 2.0 domains particularly focused on inner setting variables including access to knowledge, culture, relational connections, compatibility, and structural characteristics, the analysis will also capture inductive, emergent themes. The analysis team will read a subset of transcripts to pilot the template and establish agreement and consistency among team members. Each transcript will be summarized independently by two members and then summaries will be reconciled until consensus is reached. The summaries will be entered into a matrix organized by the same domains and each domain will be analyzed vertically through analytic memos shared and discussed with the team. Ongoing feedback will be shared through external facilitation with HV supervisors (i.e., internal facilitators) to inform real-time adaptions to facilitation. In addition, the research team will conduct a *thematic analysis* that will allow for greater depth of analysis that can inform our understanding of the implementation outcomes by incorporating questions about differences in delivery and health outcomes for different populations in different contexts. The research team will read a subset of transcripts to generate a preliminary codebook, which the team will use to code a subset of three interviews independently and compare coding and examine agreement. We will conduct thematic analysis of each transcript independently to identify theoretical domains and constructs and to identify patterns. Once the threshold is reached, all subsequent coding will be performed by two coders.

### Quantitative component

#### Education and implementation questionnaires

We will use the validated baseline and follow-up education and retention questionnaire developed by the MB trainers [25] to assess knowledge and attitudes about MB and perceived self-efficacy among all the home visitors. We will also use a 5-item REDCap questionnaire for the home visiting supervisors (participating in the CRT) that will include closed questions about number of home visitors supervised, hours spent on supervision/facilitation, and open-ended questions about challenges and opportunities around supervision and additional support and resources needed. Fidelity will be assessed using the MB Home Visitor Fidelity Rating Form, which will be completed by the home visitors after each session.

#### Home visit documentation

We will leverage the DAISEY data system currently used by IDHHS which contains a home visit record form, completed within 48 h of a home visit [60]. We will develop a similar system to collect the same data from the Indiana HVPs.

##### Geospatial data

We will use the publicly available environmental justice screening and mapping tool (EJSCREEN), developed, and maintained by the Environmental Protection Agency (EPA). This nationally consistent dataset and methodology will allow us to calculate "EJ indexes" which assess the cumulative impact of environmental exposures (i.e., pollution, land use, green space, etc.) together with health and social vulnerabilities based on participant zip codes [61, 62]. EJ indexes will be our proxy variable for structural bias, which encompasses the complex interplay of systems that reinforce and perpetuate discrimination including housing, health care access, environmental exposures, etc. [63]. These geospatial indicators will provide quantifiable, intersectional contextual data as the critical and inextricable third variable in our model to help us understand how environmental and structural factors mediate or moderate both our implementation but also our clinical health outcomes [64]. These variables align with contextual variables with the CFIR outer setting domain, including financing, systemic conditions, policies and laws, and partnerships and connections [30].

In the analysis of cluster randomized trials, the generalize linear mixed model with the logit link function will be used to assess the effect of the adapted facilitation on implementation outcomes adoption and fidelity. We will include context specific variables (Table 1) in the model including type of HVP model, funding mechanism, EJ indices, and patient characteristics (race, age, geographic location) to identify the mediating or moderating effects. To account for the intracluster correlations, we include random effects for the level of home visitor and recipient in the model. Intent-to-treat analyses will be conducted on all those in the CRT. We will also examine implementation outcomes among home visitors that are not part of the CRT because their supervisor declined to participate and determine which contextual factors contribute to 1) participation in the trial; and 2) adoption and fidelity outcomes compared to the control and intervention arms of the CRT.

**Table 1 Tab1:**
[figure not shown]
Measures, definitions, instruments, and sources

##### Power analysis

We defined cluster size (K) as the total number of HV recipients across home visitors within each supervisor. Given the K = 25, we calculated power based on different intracluster correlations (IC). We provided the total number of home visitor supervisors (N) required to achieve at least 90% power at a 5% Type I error rate (Table 2). We are well powered with the current number of home visitor supervisors estimated in each state to have ~ 100 per arm. Based on the work of Tandon et al. where the fidelity was ~ 35% we estimated the power needed to increase fidelity to 50%. The numbers were not drastically affected when changing K to 15 or 20.

**Table 2 Tab2:** Power analysis for aim 2

IC	50% vs 35%
0.1	64
0.2	106
0.3	150
0.4	190
0.5	232

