One such intervention that has proven to be particularly effective is Mothers and Babies (MB). MB is a well-supported, evidence-based cognitive behavioral intervention with demonstrated efficacy and effectiveness in reducing depressive symptoms and preventing perinatal depressive episodes among perinatal women [2, 11, 12]. Randomized controlled trials have shown that MB can prevent the onset of major depression, reduce depressive symptoms, and improve mood management in perinatal women. The most recent of these trials assessed the MB intervention one-on-one as delivered by trained lay health workers conducted in the setting of HVPs [18, 21–24]. In a type 2 hybrid implementation-effectiveness trial, even though less than 50% of eligible pregnant people received MB, participants who received at least one session of the MB intervention had better scores on the Beck Depression Inventory II (BDI) and the Perceived Stress Scale (PSS) than did control participants. While results showed the intervention was most effective when the participants received the full dose, only 34% of participants received MB without fidelity-inconsistent adaptations [25]. They concluded using evidence-based strategies that tailor implementation to the needs of specific populations and context could improve fidelity and adoption.

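### Table 2 counts every recipient under a supervisor, but fidelity is scored only where Mothers and Babies is delivered; K and the adequate-power claim for Aim 2 should be restated

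*Protocol article*

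**What the plan says.** The Aim 2 power analysis defines "cluster size (K) as the total number of HV recipients across home visitors within each supervisor" and sets it at 25. The planning contrast comes from the earlier hybrid trial: "where the fidelity was ~ 35% we estimated the power needed to increase fidelity to 50" percent. Table 2 gives the total number of supervisors for 90% power at 5% type I error as 64, 106, 150, 190 and 232 for IC 0.1, 0.2, 0.3, 0.4 and 0.5. The text says the trial is well powered with about 100 supervisors per arm, and that changing K to 15 or 20 made no drastic difference.

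Three other places bear on the denominator:

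- Background, on the earlier trial: "even though less than 50% of eligible pregnant people received MB", and "only 34% of participants received MB without fidelity-inconsistent adaptations".
- Education and implementation questionnaires: home visitors complete the fidelity rating form after each session.
- The analysis paragraph placed under Geospatial data: "Intent-to-treat analyses will be conducted on all those in the CRT".

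**The concern.** A form completed after each session produces no rating for a woman who receives no session. K = 25 nevertheless counts every recipient under the supervisor, and the power section makes no allowance for non-receipt. The trial that supplied the control rate had receipt below 50%, so the number of women per supervisor who contribute fidelity data could be about 12 or fewer. The article's check at K = 15 and 20 does not reach that low.

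The section also does not say whether the 35% is a share of all women or of women who received MB. The rate and K may therefore sit on different denominators. Table 2 is the only power statement for the implementation outcomes, and the conclusion drawn from it carries no IC limit.

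**Working it through.** **Inputs.** From the article: 35% versus 50%; K = 25; IC 0.1 to 0.5; 90% power; 5% type I error; 1:1 allocation; about 100 supervisors per arm. Assumed: a two-sided test (the article does not say, but a one-sided test fails to reproduce Table 2 at every IC); 200 supervisors in total; receipt of 50%, 40% or 30% (the article gives only an upper bound of 50%).

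**Formula.** Per arm before clustering, n = (1.960 + 1.282)² × [p₁(1−p₁) + p₂(1−p₂)] / (p₁−p₂)² = 10.507 × (0.2275 + 0.2500) / 0.15² = 223.0. Total supervisors N = 2 × ceiling{ n × [1 + (K−1) × IC] / K }.

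**Step 1: reproduce Table 2 (K = 25).** At IC 0.1: 223.0 × 3.4 / 25 = 30.3, so 31 per arm and 62 in total. At IC 0.5: 223.0 × 13 / 25 = 116.0 (115.96 unrounded), so 116 per arm and 232 in total. The series is 62/104/148/190/232 against the printed 64/106/150/190/232. Every row is within 2, so Table 2 contains no arithmetic error.

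**Step 2: K = recipients × receipt, still 35% versus 50%.** At 50% receipt, K = 12.5. At IC 0.1 the design effect is 1 + 11.5 × 0.1 = 2.15, and 223.0 × 2.15 / 12.5 = 38.4, so 39 per arm and 78 in total.

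| K (receipt) | N at IC 0.1/0.2/0.3/0.4/0.5 | Power (%) with 100 supervisors per arm |
|---|---|---|
| 25 (all recipients) | 62/104/148/190/232 | >99.9/99.5/96.6/91.5/85.3 |
| 12.5 (50%) | 78/118/160/200/242 | 99.9/98.8/95.3/90.0/84.0 |
| 10 (40%) | 86/126/166/206/246 | 99.9/98.4/94.6/89.3/83.3 |
| 7.5 (30%) | 100/138/176/216/254 | 99.6/97.5/93.3/88.0/82.2 |

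At 50% receipt the total rises by 16/14/12/10/10 supervisors over the first row.

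**Step 3: the largest IC at which 100 per arm reach 90%.** Setting n × [1 + (K−1) × IC] / K = 100 gives IC = (100K/223.0 − 1)/(K − 1).

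- K = 25: (11.21 − 1)/24 = 0.43
- K = 12.5: (5.61 − 1)/11.5 = 0.40
- K = 10: (4.48 − 1)/9 = 0.39
- K = 7.5: (3.36 − 1)/6.5 = 0.36

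**Step 4: sensitivity case with all recipients analysed and non-receipt counted as failure.** If the 35% is conditional on receipt and receipt is 50% in both arms, the contrast is 0.35 × 0.50 = 17.5% versus 0.50 × 0.50 = 25%. With K = 25, N = 170/288/408/526/646, and power at 100 per arm is 94/77/62/52/44%. If facilitation also lifts receipt to 60% in its arm (17.5% versus 0.50 × 0.60 = 30%), N = 66/112/158/204/248, close to Table 2.

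**The case against.** The mismatch is not proved. The Background figure is worded as a share of participants, which can mean all participants. The rate and K = 25 then agree and Table 2 stands. Table 1, which lists measures and definitions, is not visible in the text reviewed and may settle the denominator. This stands, and it is why the point depends on how fidelity is analysed.

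The receivers-only reading also changes little. Once the IC is substantial, the number of supervisors drives N, and halving K adds only 10 to 16 clusters. That stands too, and it bears out the article's remark that K matters little, although K near 12 lies outside what was checked.

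A reader might infer two stronger conclusions, and the documents support neither:

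- **That the trial is underpowered from IC 0.2 upward.** Step 4 gives that result only if three things hold together: the 35% is conditional on receipt, women without MB are scored as fidelity failures, and receipt is equal at 50% in both arms. The article states none of these. Its intent-to-treat sentence does not say how non-receipt is scored, and facilitation is meant to raise uptake as well as fidelity.
- **That a 50% target is unreachable because fewer than 50% received MB.** Receipt in an earlier trial is not a ceiling for this one. The Background also gives the two figures for differently named groups, eligible pregnant people and participants, which need not be the same women.

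Two further points reduce the weight. The Limitations section concedes that enrolment may fall short of maximum power. The wording on about 100 per arm could also mean per state, hence about 400 in total, which would cover every row for 35% versus 50%.

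**Conclusion.** The concern holds in a limited form. Table 2 is computed correctly from its inputs. However, its K counts all recipients, while the fidelity instrument yields data only where a session is delivered, and the article does not tie the 35% to either denominator. If fidelity is analysed among women who receive MB, and receipt is 40% to 50%, about 200 supervisors give at least 90% power up to IC 0.3, about 89% to 90% at IC 0.4, and 83% to 84% at IC 0.5.

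The adequate-power statement therefore needs an IC limit. It needs one even as printed, because 232 supervisors at IC 0.5 exceed 200 (about 85% power). The much larger totals in Step 4 are a conditional sensitivity case and not an established error. The conclusion rests on a two-sided test, 200 supervisors in total, and receipt rates that the article does not give beyond its upper bound.

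**What to change.** State the denominator of the fidelity outcome and put the planning rate and K on that same denominator.

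- **If fidelity is analysed among women who receive MB:** keep 35% versus 50%, set K to recipients times an assumed receipt rate, and recompute Table 2 for a stated range of receipt.
- **If all recipients are analysed with non-receipt as failure:** say so, state the assumed receipt and fidelity in each arm, say whether the 35% is already a share of all women, and recompute from those values, with Step 4 as a sensitivity case.

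Under either choice, replace the general adequate-power claim with the IC range at which the available supervisors reach 90%. For 200 supervisors and 35% versus 50%, that is up to about 0.40 at K = 12.5 and about 0.39 at K = 10. Also make clear whether about 100 per arm is a total or a figure per state. The cost is a recalculation and a slightly less favourable sentence, with no added supervisors, recipients or data collection.

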#### Clinical outcomes

We will test the hypothesis that recipients in the adapted facilitation arm have better clinical outcomes (e.g., lower depressive symptoms and perceived stress) compared to recipients receiving standard implementation of MB.

##### Data collection

Depression screening and perceived stress questionnaires. We will use similar baseline and follow-up surveys used in the effectiveness trials conducted by Tandon et al. We will harmonize with current practices being utilized among home visiting programs for depression and stress screening. We will ask that home visitors deliver both the EPDS and the Perceived Stress Scale (PSS), which is a 4-item questionnaire to their home visiting recipients as part of standard practice.

##### Statistical analysis

In the analysis of cluster randomized trials, the linear mixed model will be used to assess the effect of the adapted facilitation on each of two outcomes depressive symptoms and PSS at month 6 controlling for the baseline outcome. We will include the context specific variables mentioned in Aim 2, including the EJ indexes, and the random effects for the level of home visitor and recipient in the model. Intent-to-treat analyses will be conducted on all those in the CRT. We will also compare EPDS and PSS outcomes of those not in the CRT to both the control and intervention arms and identify the contextual factors that affect these outcomes.

##### Power analysis

We provided the total number of home visiting supervisors (N) required to achieve at least 90% power at a 5% Type I error rate (Table 3). We based our power calculations on the Tandon et al. study which found those receiving MB had Beck Depression Inventory II (BDI) and PSS scores that were 1.014 and 0.639 lower than the control group that did not receive the intervention. Because in this study all groups are receiving the intervention, we hypothesize that the adapted facilitation group will have depressive symptom scores and PSS scores that are lower (by approximately half) to the original study. We are well powered at all IC’s to detect the difference in depressive scores and at minimal IC’s for PSS.

**Table 3 Tab3:** Power analysis for aim 3

	Effect Size	
IC	EPDS (0.5)	PSS (0.3)
0.1	48	128
0.2	80	218
0.3	112	308
0.4	144	398
0.5	176	488

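### The Aim 3 effect sizes of 0.5 and 0.3 are halved score differences with no SD shown, so the claim of adequate power for depression at every IC is unsupported as written

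*Protocol article*

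**What the plan says.** The Aim 3 power analysis (under Clinical outcomes) reports that the earlier Mothers and Babies trial "found those receiving MB had Beck Depression Inventory II (BDI) and PSS scores that were 1.014 and 0.639 lower than the control group". Because both arms now receive the intervention, it expects "depressive symptom scores and PSS scores that are lower (by approximately half) to the original study". Table 3 then gives supervisor numbers under columns headed as effect sizes, EPDS 0.5 and PSS 0.3, which are "required to achieve at least 90% power at a 5% Type I error rate (Table 3"). The section concludes that the trial is well powered at every IC "to detect the difference in depressive scores and at minimal" ICs for PSS.

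The instruments to be collected are set out under Data collection: "We will ask that home visitors deliver both the EPDS and the Perceived Stress Scale (PSS), which is a 4-item questionnaire". The BDI-II is not among them. The cluster size is stated only in the Aim 2 power analysis: "Given the K = 25, we calculated power based on different intracluster correlations (IC"). That section also puts the available supervisors at about 100 per arm. The article prints no SD for EPDS, BDI-II or PSS.

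**The concern.** A score that is lower by 1.014 is, in ordinary usage, lower by 1.014 points. Half of that is a point difference too, and it becomes an effect size only after division by an SD. The table's 0.5 and 0.3 match the halved differences after rounding, so no division appears to have taken place. The depression figure has a second gap: a BDI-II difference is carried to the EPDS, a different scale, with no conversion.

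The Aim 3 hypothesis of better clinical outcomes rests on this table. If the hypothesised difference is about half a point, a null EPDS or PSS result from a trial described as well powered could be taken as evidence of no clinical benefit, although the trial may have had little chance of detecting that difference.

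**Working it through.** **Inputs.** From the Aim 3 power analysis: differences 1.014 and 0.639, halved; power 90%; type I error 5%. From the Aim 2 power analysis: K = 25 and about 100 supervisors per arm. Assumed here: a two-sided test, and K = 25 carried over to Aim 3.

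**1. Source of the effect sizes.** 1.014/2 = 0.507 and 0.639/2 = 0.3195. Rounded, these are the 0.5 and 0.3 of Table 3.

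**2. Reproducing Table 3.** Recipients per arm: n = 2(1.960 + 1.2816)² × SD²/d². Supervisors per arm: n × (1 + 24·IC)/25, rounded up. Total: twice that. For d = 0.5 and SD = 1, n = 84.06. At IC 0.1 this gives 84.06 × 3.4/25 = 11.4, so 12 per arm and 24 in total.

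| IC | EPDS, Table 3 | SD = 1 | SD = 1, doubled | SD = √2 | PSS, Table 3 | SD = 1 | SD = 1, doubled | SD = √2 |
|---|---|---|---|---|---|---|---|---|
| 0.1 | 48 | 24 | 48 | 46 | 128 | 64 | 128 | 128 |
| 0.2 | 80 | 40 | 80 | 80 | 218 | 110 | 220 | 218 |
| 0.3 | 112 | 56 | 112 | 112 | 308 | 154 | 308 | 308 |
| 0.4 | 144 | 72 | 144 | 144 | 398 | 200 | 400 | 398 |
| 0.5 | 176 | 88 | 176 | 176 | 488 | 244 | 488 | 486 |

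The standard total with SD = 1 does not reproduce the table. Doubling that total and setting SD = √2 fit equally well: each is exact in 8 of 10 cells and within 2 in the rest. Either way one constant serves both instruments, so 0.5 and 0.3 were handled as unit-free numbers.

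As a check on method, the unpooled formula for 35% versus 50% gives totals of 62/104/148/190/232, against 64/106/150/190/232 in Table 2. Table 2 therefore needs no extra doubling, and the factor of two is peculiar to Table 3.

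**3. Largest SD compatible with 90% power.** SDmax = δ / [3.2415 × √(2(1 + 24·IC)/(25c))], with c supervisors per arm. For c = 100 the bracket is 0.169, 0.263 and 0.331 at IC 0.1, 0.3 and 0.5.

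| Difference | c per arm | IC 0.1 | IC 0.3 | IC 0.5 |
|---|---|---|---|---|
| Depression, 0.507 points | 100 | 3.0 | 1.9 | 1.5 |
| PSS, 0.3195 points | 100 | 1.9 | 1.2 | 1.0 |
| Depression, 0.507 points | 200 | 4.2 | 2.7 | 2.2 |

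The rows with c = 100 assume no particular SD. The last row allows for reading about 100 per arm as a figure for each state.

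**4. Illustration under assumed SDs.** The article gives no SD, so residual EPDS SDs of 4, 5 and 6 points are assumptions. Power = Φ(δ/SE − 1.960), with SE = SD × √(2(1 + 24·IC)/(25c)). For SD 4, IC 0.1 and c = 100, SE = 0.209 and 0.5/0.209 = 2.40, so power is Φ(0.44) = 67%.

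| Power for 0.5 EPDS points | SD 4 | SD 5 | SD 6 |
|---|---|---|---|
| c = 100, IC 0.1 | 67% | 48% | 36% |
| c = 100, IC 0.3 | 34% | 23% | 18% |
| c = 200, IC 0.1 | 92% | 77% | 62% |
| c = 200, IC 0.3 | 59% | 42% | 31% |

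Using t quantiles lowers these by less than half a percentage point. For 0.3195 PSS points with c = 100, an assumed SD of 2 gives 87% at IC 0.1 and 35% at IC 0.5. An assumed SD of 3 gives 53% and 18%.

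**The case against.** **The figures may be standardised.** The article never says whether 1.014 and 0.639 are points or SD units, and the cited report is not at hand. A reader might infer a proven unit error. The text does not establish that: the points reading is a strong inference from score-scale wording. If the figures are standardised, Table 3 is conservative by a factor of about two, the depression claim holds, and borrowing an effect across depression scales is ordinary planning. This stands, and it limits the conclusion to unsupported as written.

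**No SD can be attributed to the authors.** Because √2 reproduces the table, a reader might infer that an SD of about 1.41 points was assumed. The documents do not support that either, since SD = 1 with a doubled total fits just as well.

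**The power figures depend on chosen inputs.** True: the SDs, K = 25 for Aim 3 and the 200-supervisor total are all assumptions. With about 400 supervisors, power at SD 4 and IC 0.1 reaches 92%, but it is 59% at IC 0.3 and 41% at IC 0.5, so the claim for every IC still fails at that SD. Limiting the PSS claim to minimal ICs also fits about 200 supervisors better, since Table 3 stays below 400 up to IC 0.4.

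**Baseline adjustment helps.** It does, but reducing an SD of 5 to 3.0 needs a correlation of 0.8 (√(1 − 0.8²) = 0.6), and reducing it to 1.5 needs about 0.95. No correlation is stated.

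**Aim 3 is secondary in weight.** The Conclusion section calls it exploratory, and Limitations concedes that power may fall short. That reduces the consequences. The Limitations text, however, concerns enrolment, not the effect size.

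**Conclusion.** The point holds in limited form. Table 3's effect sizes equal the halved score differences, with no SD, no standardisation and no conversion from BDI-II to EPDS, and its totals carry an unexplained factor of two common to both scales. Read as points, the depression claim at every IC up to 0.5 requires a residual SD of about 1.5 points or less with 200 supervisors, or about 2.2 with 400. Nothing printed supports either.

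A reader might go further and conclude that the trial is underpowered for Aim 3. The documents do not show that, because the size of any shortfall depends on SDs they do not give. The conclusion also rests on a two-sided 5% test, on K = 25 applying to Aim 3, and on reading the quoted differences as points.

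**What to change.** - State the SDs of the EPDS and the 4-item PSS with their source, and the baseline correlation if the calculation uses one.
- Convert the hypothesised point differences to standardised effects on the instruments actually collected, and justify the step from BDI-II to EPDS.
- If 1.014 and 0.639 were already standardised, say so and show it.
- Recompute Table 3, state the cluster size used for Aim 3, and explain or remove the factor of two.
- Say whether about 100 supervisors per arm is a figure for each state or overall.
- Replace the claim of good power at every IC with the power, or the detectable point difference, at the planned number of supervisors. With 100 per arm the detectable difference at 90% power is 0.17, 0.26 or 0.33 SD at IC 0.1, 0.3 or 0.5.

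The cost is one recalculated table and one reworded claim. Enrolment, conduct and analysis stay as they are. The only downside is that the stated power may become less favourable.
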